## 10.2 Causality

The relationship of each adverse event to the trial medication must be determined by a medically qualified individual (the Country CI or delegate) according to the following definitions:

- reasonable possibility
- no reasonable possibility

All AEs (SAEs) labelled reasonable possibility of a causal relationship to the IMP will be considered as related to the IMP.

### 10.3 Adverse Event Reporting

An adverse event is any condition that occurs after enrollment, whether or not considered related to study treatment. Signs and symptoms existing prior to study and documented on the baseline Medical History form or Physical Examination Form are not considered AEs. Only baseline signs and symptoms that worsen while the subject is on the study drug are considered adverse events.

At every visit, participant will be questioned regarding the occurrence and nature of any adverse experiences. If any signs, symptoms or the results of the laboratory tests indicate an adverse effect, the study physician should determine the severity (grade) of the AE and judge the relationship to the study treatment. In addition, if an adverse event necessitates medical care, appropriate care will be provided. Adverse events should be documented on the Adverse Event Report form, regardless of relationship to the study drugs. Notably, AEs thought to be due to treatment with the study drug are still reported as AEs in this study. The following information will be collected for all Adverse Events:

- Start and stop dates
- Severity (See the Severity Grading section below)
- Relationship to study drugs (See the Association with the Study Drug below )
- Action taken with study drugs
- Treatment for the AE and outcomes

The only circumstance in which an Adverse Event Report Form will not be filled out will be isolated lab value abnormalities of grade 1 severity.

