#### 5. Benefit/ Risk

##### Benefit

- At the individual level:

Our recent works on the identification of nephrotoxic autoantibody activity should contribute to improve the individual management of patients with MN, and help to better select patients who should benefit from early and aggressive immunosuppressive strategies. Patients in the personalized arm should expect a remission rate around 85% at 12 months.

- At the collective level:

If the personalized strategy is validated, we should improve the remission rate and decrease the risk of serious adverse events in iMN treatment. Moreover, ancillary studies will help us to understand resistant forms of iMN and proposed new immune therapy like inducing TReg therapy, or Memory B-cell targeting in recurrent forms.

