#### **8.4 Frequency of follow-up visit-protocol**

After randomization, all patients will be scheduled at M3, M6, M9, M12, M18 and M24 post-treatment for a routine follow-up, and benefit from a symptomatic antihypertensive and antiproteinuric treatment throughout the study period according to the KDIGO guidelines.

In the GEMRITUX group: at M6, if the patient exhibits an active disease (UPCR remains  $> 3.5$  g/g and albuminemia  $< 30$  g/l), they will receive two 375 mg/m^2 rituximab infusions at 1-week interval.

In the personalized group, rituximab injections should be scheduled between 5 and 14 days after randomization in case the epitope results are in favor for immunosuppressive treatment, as follows:

- at M0 and M6, if the patient exhibits anti-PLA2R1 anti-CTLD1 or CTLD7 activity, they will receive two 1 g infusions at 2-week interval.
- At M6, if a patient has an active disease/ anti-PLA2R1 ab + or if he has an active disease /anti-PLA2R1 Ab –, symptomatic treatment should be optimized. And if he exhibits anti-CysR restricted activity with active disease (UPCR remains  $> 3.5$  g/g and albuminemia  $< 30$  g/l), they will receive two 375-mg/m^2 rituximab infusions at 1-week interval.

[figure not shown]

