## 9. Treatment

### 9.1 Study treatment

#### - Investigational Product

The investigational product rituximab will be stored in a secure area according to local regulations. It will be the responsibility of the investigator to ensure that investigational product is only

dispensed to study subjects. The investigational product will be dispensed only from official study sites by authorized personnel according to local regulations.

Rituximab will be delivered at two different doses according to the arm of the protocol: 1g J0 and J15 in the personalized arm with anti-CTLD1/7 activity or 375 mg/m^2 J0 and J7 in the personalized arm with anti-CysR activity and active disease at M6 or in the GEMRITUX arm with active disease.

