## **9.2 Medical treatment common to both arms of the study: Nephro-protective treatment**

The KDIGO 2012 recommendations for the management of nephrotic syndrome will be followed:

First line RAAS blockade with an angiotensin-converting enzyme inhibitor (ACEI) or an angiotensin 2 receptor antagonist and diuretic up-titration.

Double RAAS blockade could be indicated under close monitoring.

Drugs employed for the symptomatic treatment are those uses in usual practice. Each center will be referring to the internet website: <http://base-donnees-publique.medicaments> for adapting the contraindications, contraception, monitoring of patients and prohibit drugs in accordance with the study (annexe 1).

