## 10. Reporting adverse events (AEs) and serious adverse events (SAEs)

### 10.1 Definitions

|                             |                                                                                                                                                                                                                                                                                                                                                                                                                                                                                                                                                                                                             |
|-----------------------------|-------------------------------------------------------------------------------------------------------------------------------------------------------------------------------------------------------------------------------------------------------------------------------------------------------------------------------------------------------------------------------------------------------------------------------------------------------------------------------------------------------------------------------------------------------------------------------------------------------------|
| Adverse Event (AE)          | Any untoward medical occurrence in a participant to whom a medicinal product has been administered, including occurrences that are not necessarily caused by or related to that product.                                                                                                                                                                                                                                                                                                                                                                                                                    |

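### Section 10.3 counts worsening of a baseline sign as an adverse event only while on rituximab, so before M6 it can be recorded for no control patient but for about 70% of the personalised arm

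*Protocol*

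**What the plan says.** Section 10.3 opens with a rule that does not depend on treatment: "An adverse event is any condition that occurs after enrollment, whether or not considered related to study treatment". Its second sentence sets aside signs and symptoms already documented on the baseline history or examination form. Its third brings them back only under a condition: "Only baseline signs and symptoms that worsen while the subject is on the study drug are considered adverse events".

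Section 9.1 identifies the study drug: "The investigational product rituximab will be stored in a secure area according to local regulations". The supportive drugs have their own section, 9.2, headed "Medical treatment common to both arms of the study: Nephro-protective treatment", so they are not what puts a patient on study drug.

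Exposure to rituximab differs by arm by design. In the personalised arm, for patients whose epitope result calls for it, section 8.4 says "rituximab injections should be scheduled between 5 and 14 days after randomization". For the comparator, rituximab first becomes possible later: "In the GEMRITUX group: at M6, if the patient exhibits an active disease". Under section 8.5, personalised-arm patients with CysR-restricted activity follow the same six months of symptomatic treatment as controls.

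Section 2.2 lists the recording of all AEs and SAEs over 24 months as objective 9, among the objectives that compare the two strategies.

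**The concern.** A rule that admits an event only during exposure is harmless when both arms are exposed alike. Here exposure is what the strategies vary, so the rule opens the recording window at different times in the two arms.

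Patients enter with nephrotic syndrome, and oedema, weight and blood pressure are examined at M0. Many will therefore have a baseline sign that can worsen. Suppose oedema is moderately worse at M3 in two patients, one control and one personalised-arm patient infused after M0. Under the third sentence of 10.3 the first is not an adverse event and the second is. Under the first sentence, both could be. The trial is open label, so the site knows which patients have been infused and can apply either sentence.

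What is at stake is the adverse event table. The definition alone could make the early-treatment strategy look worse than the symptomatic phase it replaces. An analysis plan cannot repair this, because an event never entered as an AE cannot be recovered at analysis.

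**Working it through.** The protocol states no figure on this point, so there is none to reproduce. The check is how many patients the third sentence of 10.3 can reach before M6, and what that does to the counts.

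**Inputs from the protocol**

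- Total sample 64 (section 7.2), allocated 1:1 (section 8.3): 64 / 2 = 32 per arm.
- Share with CTLD1/7 activity about 70%, CysR-restricted about 30% (section 7.1).
- First possible rituximab: M6 for controls and CysR-restricted patients; 5 to 14 days after randomisation for personalised-arm patients with CTLD1/7 activity (sections 8.4 and 8.5).

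**Step 1. Patients who can be on study drug before M6**

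- Control: 0 of 32.
- Personalised: 0.70 × 32 = 22.4, about 22 of 32. If the CTLD1/7 share were 60% to 80%: 0.60 × 32 = 19.2 to 0.80 × 32 = 25.6, about 19 to 26.
- Personalised, off drug like the controls: 0.30 × 32 = 9.6, about 10 of 32.

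**Step 2. Effect on recorded counts**

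Let w be the true proportion of patients with a non-serious worsening of a baseline sign before M6, set equal in both arms to isolate the effect of the definition. The protocol gives no value for w, so 10% to 40% is an assumed range. Patients infused after M0 are treated as on drug until M6, and the few days before the first infusion are ignored.

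- Counting from randomisation in both arms: 32 × w per arm.
- Third sentence of 10.3, control: 0 × w = 0.
- Third sentence of 10.3, personalised: 0.70 × 32 × w = 22.4 × w.

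| w | Equal counting, each arm | 10.3 literal, control | 10.3 literal, personalised |
|---|---|---|---|
| 10% | 3.2 | 0 | 2.2 |
| 20% | 6.4 | 0 | 4.5 |
| 30% | 9.6 | 0 | 6.7 |
| 40% | 12.8 | 0 | 9.0 |

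Both arms are under-counted, but unequally, and the whole apparent difference comes from the wording.

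**Step 3. How firm the window is**

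Section 10.3 does not say what being on the drug means for a course of two infusions. Section 1.3 reports residual rituximab in some patients up to 6 to 9 months after the first infusion. A narrower reading, such as the infusion period only, would lower the personalised counts in the last column. The control count before M6 stays at 0 on any reading.

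**Step 4. What the sentence does not reach**

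- Serious events: the SAE definition in 10.1 carries no drug condition.
- New events: the first sentence of 10.3 counts them from enrolment.
- Laboratory results: 10.3 treats them in a separate sentence, and its stated exemption from an AE form covers only isolated grade 1 laboratory abnormalities.
- Dialysis, cardiovascular events and deaths: section 14 sends them to the monitoring committee without regard to arm or exposure.
- Severe infection: section 12.3.2 compares it over all follow-up, with no exposure restriction.

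**The case against.** The strongest reply is that this is a wording inconsistency of small reach. It concerns only non-serious worsening of a sign already on the baseline form. Oedema, weight, blood pressure, blood and urine results are recorded at M3 and M6 in both arms anyway, and proteinuria, creatinine and eGFR are compared between arms as secondary outcomes from M6. The only safety comparison with a specified test, severe infection, is untouched. From M6, control patients with active disease also receive rituximab, so the gap narrows. All of this stands, and it limits the point to the descriptive AE comparison.

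It does not remove the point. Objective 9 covers all AEs, not only severe infections. A blood pressure entry in the visit data is not an adverse event with grade, causality and outcome. The AE definition in 10.1, "Any untoward medical occurrence in a participant to whom a medicinal product has been administered", does not settle the matter either: supportive drugs are medicinal products too, so it fits patients in both arms and gives a site no reason to follow the third sentence of 10.3 rather than the first.

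Three stronger readings are tempting and should not be drawn:

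- *Worsening is counted in one arm and not in the other.* About 30% of the personalised arm is also off drug before M6, so the contrast is 0% against about 70%.
- *Declining renal function or low albumin during the symptomatic phase is defined away.* The restriction concerns signs and symptoms; laboratory findings fall under a different sentence of 10.3.
- *The expected benefit in section 5, that "we should improve the remission rate and decrease the risk of serious adverse events in iMN treatment", can no longer be assessed.* SAEs are defined without reference to study drug, so this does not follow.

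**Conclusion.** The point holds in a limited form. Section 10.3 contradicts itself, and its third sentence, followed literally, makes the recording of worsened baseline signs depend on an exposure that differs by arm. Before M6 the rule can reach 0 of 32 controls and about 22 of 32 personalised-arm patients (19 to 26 for a CTLD1/7 share of 60% to 80%). With equal true worsening of 10% to 40%, recorded counts would be 0 against about 2.2 to 9.0. The bias runs against the personalised strategy.

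The 0 of 32 follows from the treatment schedule alone. The 22 of 32 rests on the protocol's own 70% estimate. The event counts rest on an assumed worsening rate and on treating patients as on drug from first infusion to M6, so they illustrate the mechanism and do not forecast results. The primary endpoint is not involved.

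**What to change.** Reconcile the third sentence of section 10.3 with the first. For example: *Baseline signs and symptoms that worsen after randomisation are adverse events, in both arms and whether or not study drug has been given.* State one counting period, randomisation to M24, for both arms, and carry the same wording into the e-CRF guidance. This also removes the need to define what being on the drug means for a two-infusion course.

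The cost is one protocol sentence and its e-CRF counterpart, plus a few more AE entries from patients not yet given rituximab, that is, controls and CysR-restricted patients before M6. No treatment or visit changes. Whether the tables are then split at M6 is a reporting choice that can be left to the analysis plan.

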#### Severity Grading

For evaluation and reporting purposes, events will be graded by using CTCAE v5.0.:

Grade refers to the severity of the AE. The CTCAE displays Grades 1 through 5 with unique clinical descriptions of severity for each AE based on this general guideline:

- **Grade 1** Mild; asymptomatic or mild symptoms; clinical or diagnostic observations only; intervention not indicated.

- **Grade 2** Moderate; minimal, local or noninvasive intervention indicated; limiting age-appropriate instrumental ADL\*.
- **Grade 3** Severe or medically significant but not immediately life-threatening; hospitalization or prolongation of hospitalization indicated; disabling; limiting self care ADL\*\*.
- **Grade 4** Life-threatening consequences; urgent intervention indicated.
- **Grade 5** Death related to AE.

#### **Activities of Daily Living (ADL)**

\*Instrumental ADL refer to preparing meals, shopping for groceries or clothes, using the telephone, managing money, etc.

\*\*Self care ADL refer to bathing, dressing and undressing, feeding self, using the toilet, taking medications, and not bedridden.

### **10.4 Association with the Study Drug**

- Association with the use of the study drug means that there is a reasonable possibility that the adverse event may have been caused by the drug under investigation. All adverse events are graded with regard to their association with the use of the study drug. The classifications used includes reasonable possibility or no reasonable possibility of a causal relationship to the IMP.

### **10.5 SAE and SUSAR Reporting Procedure**

#### **Electronic database for safety reporting**

1. The European Medicines Agency established by Regulation (EC) No 726/2004 (the 'Agency') shall set up and maintain an electronic database for the reporting.
2. The Agency shall, in collaboration with Member States, develop a standard web-based structured form for the reporting by sponsors to the database referred to in paragraph 1 of suspected unexpected serious adverse reactions.

#### **Reporting of adverse events and serious adverse events by the investigator to the sponsor**

The investigator shall record and document adverse events or laboratory abnormalities identified in the protocol as critical to the safety evaluation and report them to the sponsor in accordance with the reporting requirements and within the periods specified in the protocol.

The investigator shall record and document all adverse events, unless the protocol provides differently. The investigator shall report to the sponsor all serious adverse events occurring to subjects treated by him or her in the clinical trial, unless the protocol provides differently.

The investigator shall report serious adverse events to the sponsor **without undue delay** but not later than within 24 hours of obtaining knowledge of the events, unless, for certain serious adverse events, the protocol provides that no immediate reporting is required. Where relevant, the investigator shall send a follow-up report to the sponsor to allow the sponsor to assess whether the serious adverse event has an impact on the benefit-risk balance of the clinical trial.

The sponsor shall keep detailed records of all adverse events reported to it by the investigator.

If the investigator becomes aware of a serious adverse event with a suspected causal relationship to the investigational medicinal product that occurs after the end of the clinical trial in a subject treated by him or her, the investigator shall, without undue delay, report the serious adverse event to the sponsor.

All serious adverse events (SAE) must be reported by the investigator to the sponsor's service in charge of safety (Vigilance):

Clinical Trials Vigilance: [name], CHU de Nice; [contact]; [contact];  
email: [contact]

#### **10.6 Reporting of suspected unexpected serious adverse reactions by the sponsor to the Agency**

1. The sponsor performed in at least one Member State shall report electronically and without delay to the database all relevant information about the following suspected unexpected serious adverse reactions:

(a) all suspected unexpected serious adverse reactions to investigational medicinal products occurring in that clinical trial, irrespective of whether the suspected unexpected serious adverse reaction has occurred at a clinical trial site in the Union or in a third country;

(b) all suspected unexpected serious adverse reactions to investigational medicinal products occurring in any of the subjects of the clinical trial, which are identified by or come to the attention of the sponsor after the end of the clinical trial.

2. The period for the reporting of suspected unexpected serious adverse reactions by the sponsor to the Agency shall take account of the seriousness of the reaction and shall be as follows:

- (a) in the case of fatal or life-threatening suspected unexpected serious adverse reactions, as soon as possible and in any event not later than seven days after the sponsor became aware of the reaction;
- (b) in the case of non-fatal or non-life-threatening suspected unexpected serious adverse reactions, not later than 15 days after the sponsor became aware of the reaction;
- (c) in the case of a suspected unexpected serious adverse reaction which was initially considered to be non-fatal or non-life threatening but which turns out to be fatal or life-threatening, as soon as possible and in any event not later than seven days after the sponsor became aware of the reaction being fatal or life-threatening.

Where necessary to ensure timely reporting, the sponsor may submit an initial incomplete report followed up by a complete report.

3. Where a sponsor, due to a lack of resources, does not have the possibility to report to the database referred to in Article 10.5.1 and the sponsor has the agreement of the Member State concerned, it may report to the Member State where the suspected unexpected serious adverse reaction occurred. That Member State shall report the suspected unexpected serious adverse reaction.

#### **10.7 Exception rules for SAE reporting**

Exceptions to immediate SAE reporting are applied if hospitalization is the only criterion for SAE classification and the below listed criteria are met.

SAE's are not reported (but are documented as AE's if they meet the AE documentation criteria) if the only reason of SAE classification is:

- o hospitalizations planned before entry into the clinical study
- o elective treatment of a pre-existing condition
- o routine treatment not associated with any deterioration in condition.

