## 2.2 Secondary Objectives

The following objectives are to compare between a personalized treatment of iMN driven by anti-PLA2R1 antibody epitope profiles and the GEMRITUX therapeutic protocol:

1. Complete clinical remissions at M6, M9, M12, M18, M24
2. Partial clinical remission at M6, M9, M12, M18, M24
3. Immunological remissions at M6, M9, M12, M18, M24
4. Proteinuria and albuminuria at M6, M9, M12, M18, M24
5. Changes in proteinuria and albuminuria from baseline at M6, M9, M12, M18, M24
6. Serum creatinine and estimated glomerular filtration rate (eGFR) at M6, M9, M12, M18
7. Changes in serum creatinine and eGFR from baseline at M6, M9, M12 and M18
8. PLA2R1-Ab titers at M6, M9, M12, M18 and M24
9. Recording all AEs/SAEs during study follow-up, 24 months

The following objectives aim to study risk factors for remission or relapse:

10. To determine risk factors for remission (immunological and clinical, partial or complete) at M12 in patients pooled from the two arms
11. To determine risk factors for relapse (between M12 and M24) in patient responders at M12, pooled from the two arms

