| Adverse Reaction (AR)       | 
An untoward and unintended response in a participant to an investigational medicinal product, which is related to, any dose administered to that participant.
 
The phrase "response to an investigational medicinal product" means that a causal relationship between a trial medication and an AE is at least a reasonable possibility, i.e. the relationship cannot be ruled out.
 
All cases judged by either the reporting medically qualified professional or the Sponsor as having a reasonable suspected causal relationship to the trial medication qualify as adverse reactions.
 |
| Serious Adverse Event (SAE) | 
A serious adverse event is any untoward medical occurrence that:
 
 
Results in death
 
Is life-threatening
 
Requires patient hospitalisation or prolongation of existing hospitalisation
 
Results in persistent or significant disability/incapacity
 
Consists of a congenital anomaly or birth defect.
 
                                                                                                                                                                                                                |

|                                                       |                                                                                                                                                                                                                                                                                                                                                                                                                                                       |
|-------------------------------------------------------|-------------------------------------------------------------------------------------------------------------------------------------------------------------------------------------------------------------------------------------------------------------------------------------------------------------------------------------------------------------------------------------------------------------------------------------------------------|

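### The elective-treatment exemption in Protocol Section 10.7 does not exclude membranous nephropathy or its worsening, so a planned admission for worsened disease can go unreported as an SAE

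*Protocol*

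**What the plan says.** Section 10.1 of the Protocol makes an event serious if, among other criteria, it "Requires patient hospitalisation or prolongation of existing hospitalisation". Section 10.7 then carves out exceptions. It opens with "Exceptions to immediate SAE reporting are applied if hospitalization is the only criterion for SAE classification" and continues that "SAE's are not reported (but are documented as AE's if they meet the AE documentation criteria" are met, where the sole reason for the SAE label is one of three items. These are stays planned before study entry, "elective treatment of a pre-existing condition", and "routine treatment not associated with any deterioration in condition".

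Section 10.3 governs what counts as an AE when a sign or symptom was already present at entry: "Only baseline signs and symptoms that worsen while the subject is on the study drug are considered adverse events".

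Section 2.2 places "Recording all AEs/SAEs during study follow-up, 24 months" ninth among the items to be compared between the two strategies, and the Summary also lists serious adverse events among the comparisons. Section 5 states that, if the strategy is validated, "we should improve the remission rate and decrease the risk of serious adverse events in iMN treatment".

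**The concern.** Nephrotic MN with anti-PLA2R1 antibodies is an entry requirement, so it is a pre-existing condition in all 64 patients. An exemption for elective treatment of any pre-existing condition therefore takes in the disease under study unless the text says otherwise, and it does not. The condition that there be no deterioration appears in the third bullet only. A site applying the second bullet by itself could exempt a planned admission made because MN has got worse since randomisation.

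At stake are prompt notification of such events to the sponsor's vigilance service and the completeness of the SAE counts behind objective 9. Disease-driven admissions are also among the events that bear on the SAE benefit hoped for in Section 5.

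**Working it through.** There is no stated figure to reproduce. The check sets the passages side by side and then does simple arithmetic on who is exposed.

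**1. Can a disease-driven planned admission meet the exemption?** Take a planned stay for resistant oedema after randomisation.
- Pre-existing condition: yes, by the inclusion criteria (Section 6.1).
- Elective: yes, if planned.
- Hospitalisation the only seriousness criterion: possible.
- No-worsening limit in the second bullet: none.
- Exclusion of the disease under study: none.

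All conditions can be met, so the stay can leave SAE reporting.

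**2. Is it then kept as an AE?** Section 10.7 keeps it only if AE documentation criteria are met. Section 10.3 opens broadly (any condition arising after enrolment, related or not) but limits worsening of baseline signs to time on study drug. Section 9.1 names rituximab as the investigational product. Under Sections 8.4 and 8.5, controls receive none before M6, and nor do personalised patients with CysR-restricted activity. AE capture for these patients is therefore uncertain rather than excluded. The visit lists in Section 8.5 and the schedule of assessments name serious adverse events only, so they add no separate prompt for other AEs.

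**3. What is not lost?** Unplanned admissions are not elective. Events serious on any other criterion stay reportable. Dialysis, the listed cardiovascular events and deaths go on a specific form to the committee described in Section 14, and Section 10.8 lists dialysis among the expected disease-linked events.

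**4. Who is exposed?** Inputs: 64 patients randomised 1:1, so 32 per arm; 30% CysR-restricted (Section 7.1); expected M12 remission of 80% personalised (7.1) and 45% control (7.2).
- Without rituximab, M0 to M6: controls 32; personalised 32 × 0.30 = 9.6; control share 32 / 41.6 = 77%.
- Not in remission at M12: controls 32 × 0.55 = 17.6; personalised 32 × 0.20 = 6.4; control share 17.6 / 24.0 = 73%. With the 85% rate in Section 5, personalised is 32 × 0.15 = 4.8 and the share is 17.6 / 22.4 = 79%.
- Still active at M6, assuming control remission s of 10–30%, 50% remission in CysR-restricted patients, and remission r of 50–85% after the higher-dose course: controls 32(1 − s) = 22.4 to 28.8; personalised 32[0.3 × 0.5 + 0.7(1 − r)] = 8.2 to 16.0; control share 58% to 78%.
- If the exempt stays are instead planned admissions for rituximab courses, under the same assumptions: controls 22.4 to 28.8; personalised 32[0.7 + 0.3 × 0.5 + 0.7(1 − r)] = 30.6 to 38.4; control share 37% to 49%.

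The majority is in the control arm when exposure means untreated or persistent disease, and it reverses when exposure means infusion stays.

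**5. How many events?** The protocol gives no rate of planned disease-related admissions. For scale only, an assumed 5–15% of patients without rituximab in M0 to M6 gives 1.6 to 4.8 controls (32 × 0.05 to 32 × 0.15) and 0.5 to 1.4 personalised patients (9.6 × 0.05 to 9.6 × 0.15).

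**The case against.** The best defence is that a stay prompted by worsening is classed as serious because an untoward occurrence required admission, not because elective treatment took place, so the exemption was never meant to reach it. That is probably the intention, but the text does not say so, and Section 4 has 23 sites applying it. The defence reduces the point to a wording fault; it does not remove it.

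Several stronger readings are tempting and are not supported:

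- *These admissions are not counted at all.* A reader might infer this, but Section 10.7 keeps exempt events as AEs where AE criteria are met. A recorded one could still show as grade 3, since the CTCAE grading in Section 10.3 includes hospitalisation being indicated. The weakness lies in the study-drug condition of Section 10.3.
- *Planned starts of dialysis disappear.* They do not; Sections 10.8 and 14 both treat dialysis as an event. Section 10.12 says no safety board is required, which sits badly with Section 14, but the form and its routing are specified.
- *A planned between-arm test is biased.* The only test specified for objective 9 in Section 12.3.2 is on severe infections, defined in Section 3 as infections leading to hospitalisation. Those are not elective treatment of MN. The statement in Section 5 is a hoped-for benefit, not an endpoint. If losses do fall mainly on controls, they would work against the personalised arm and could not create a falsely favourable safety result for it.
- *Most affected patients are controls, as a fact.* The rule is worded identically for both arms, objective 9 runs for 24 months, and the share depends on which stays are in question.

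What remains is that Section 2.2 and the Summary list AEs/SAEs among the between-arm comparisons. The SAE count is therefore an output of the trial, and the rule feeding it has a gap.

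**Conclusion.** The rule is faulty as written, and the consequence is modest. A planned admission for MN that has worsened since randomisation, serious only through hospitalisation, need not be reported as an SAE. In a patient not yet given rituximab it may not be recorded as an AE. The damage is to SAE notification and to the AE/SAE comparison in objective 9; the primary analysis and the severe-infection test are untouched.

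More controls than personalised patients are likely to be affected, about 77% on the M0 to M6 measure. That rests on the protocol's 30% CysR share, on the time without rituximab being the relevant exposure, and on similar admission rates among patients without rituximab in either arm. The number of events cannot be derived from the document. This is a cheap improvement worth making.

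**What to change.** Three edits, affecting reporting only:

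1. In Section 10.7, limit the second bullet to elective treatment of a condition other than membranous nephropathy or its complications that existed before entry and has not worsened since randomisation.
2. In the same section, state that admission solely to give a protocol-scheduled infusion is exempt, so that edit 1 does not turn infusion stays into SAEs. The third bullet arguably covers this already, but it should be explicit.
3. In Section 10.3, make worsening of baseline signs or symptoms after randomisation an AE in both arms, whether or not rituximab has been given.

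While editing Section 10.7, also settle whether the exception is from immediate reporting only, as its first sentence says, or from SAE reporting altogether, as its second says.

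The cost is a few lines of text and a few more SAE and AE forms.
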